This proposed feasibility study will evaluate a diagnostic-CT-enabled planning workflow and assess efficacy, acceptability and scalability. The workflow will employ CBCT-planning as a back-up pathway and incorporate optical surface guidance for ease of set-up reproducibility. The study will also expand eligibility criteria from previous work to include thoracic disease targets in addition to bone and soft tissue disease. Pain response or treatment response were not chosen as endpoints given previous evidence of equivalency and/or the reasonable assumption of equivalency as both arms of the investigation ultimately receive the same treatment. The only difference between arms is the planning image set. Thus, the evaluation of the efficacy of the diagnostic-CT-enabled planning workflow, in this context, is dependent upon the rate of plan deliverability (i.e. the experimental planning arm produced a deliverable plan) and acceptability (i.e. the experimental planning arm produced a plan determined to be acceptable as per institutional guidelines).

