##### Undeliverable plan

Plans may be deemed undeliverable in the following scenarios:The treatment position could not be reproduced within tolerance *and* there is significant anatomical or external contour variation that cannot be corrected with IGRTProgression has occurred such that the target volume requires expansion for adequate coverageChanges are observed on CBCT that contraindicate PRTCBCT reveals new findings such as interval development of pathological fracture, atelectasis, etc. which warrant PRT deferral for further assessment or involvement of other services

At the discretion of the RO, CBCT-enabled planning may be enacted if a diagnostic-CT-enabled plan is considered undeliverable. This process is described in the next section.

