##### Treatment delivery with CBCT plan

If the treating RO decides to engage this process, a DART-team medical physicist will be paged to the unit immediately to import/register/prepare the CBCT acquisition for planning. While the plan is generated, the patient can stay on the treatment bed or wait in the unit waiting area. The RO will re-contour the target on the CBCT and delineate field borders/shielding. The medical physicist will generate a simple plan for immediate RO approval and perform the required physics QA. A unit therapist will then perform new case QA. The patient can then be treated using the CBCT plan after repeat CBCT for verification.

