#### Plan deliverability

Plan deliverability will be reported as either yes or no. *Primary Plan Deliverability* will refer to the deliverability of the diagnostic-CT-enabled treatment plan. *Secondary Plan Deliverability* will refer to the deliverability of the CBCT-based plan in cases where a CBCT-based plan is generated.

For any undeliverable plan, the RO must document the reasons why the plan was undeliverable and the PI must be alerted within 24 hours.

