#### Plan acceptability

Plan acceptability will be determined by blinded RO review, performed by an expert panel comprised of RO members from the local Palliative Disease Site Team. Because a review of the *planned* dose distribution would not preserve blinding due to visibly apparent characteristics of CT/CT simulation imaging, plan acceptability will be assessed by review of dose distribution of the *delivered* plan shown on the fraction 1 image matching CBCT.

Plan acceptability is defined according to the following local criteria for simple palliative planning:*For parallel-opposed pair plans:*Adequate (as per RO discretion) coverage of the target volume (PTV) by the 90% isodose lineHot spot (maximum point dose) is ≤115% of prescribed dose OR if hot spot is > 115% then the total volume of the hot spot should be <2cm^3^*For single direct field plans:*Adequate (as per RO discretion) coverage of the target volume (PTV) by the 80% isodose lineHot spot (maximum point dose) is ≤125% of prescribed dose OR if hot spot is > 125% then the total volume of the hot spot should be <2cm^3^

Blinded-reviewers will ascribe a score of 1, 2 or 3 to each plan based on the following criteria:AcceptableMinor deviation but still acceptableUnacceptable – plan deficiency may impact clinical outcome

Plan acceptability *does not* refer to clinical judgements such as target delineation, beam arrangement, energy, field borders, shielding, dose/fractionation, etc.

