### Statistical analysis plan

Patients will be analyzed in the groups to which they are assigned (intention-to-treat). Comparisons between treatment arms for TIC (primary endpoint) will be performed using the two-sample t-test. TIC data is anticipated to be normally distributed. In the event such data is not normally distributed, non-parametric testing using the Wilcoxon rank sum test will be substituted as appropriate. For the secondary endpoints for efficacy (rate of plan deliverability and rate of plan acceptability on blinded review of dose distributions) and acceptability (stakeholder evaluations based on Likert scale), differences between treatment arms will be compared using the Chi-square test or Fisher’s exact test as appropriate. For the secondary endpoint for scalability based on the ISAT, differences between treatment arms will be compared using the two-sample t-test or substituted with Wilcoxon rank sum test if such data is not normally distributed, similar to primary endpoint.

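### Plan acceptability is scored on the delivered plan, so the between-arm comparison depends on deliverability in Arm 2 only and may mix in CBCT back-up plans

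*Protocol article*

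**What the plan says.** Under Plan acceptability, the protocol article states that "plan acceptability will be assessed by review of dose distribution of the" delivered "plan shown on the fraction 1 image matching CBCT". The reason given is blinding: the planned distribution would show reviewers which kind of CT had been used.

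Under Undeliverable plan, which sits in the Arm 2 workflow, four situations are listed. In those, "CBCT-enabled planning may be enacted if a diagnostic-CT-enabled plan is considered undeliverable", at the oncologist's discretion. The section Treatment delivery with CBCT plan then says: "The patient can then be treated using the CBCT plan after repeat CBCT for verification".

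Under Plan deliverability, the two kinds of plan are kept apart. Primary deliverability concerns the diagnostic-CT plan, and secondary deliverability "will refer to the deliverability of the CBCT-based plan in cases where a CBCT-based plan is generated". The acceptability section makes no such split.

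The Background says that only the planning image set differs between arms. It ties efficacy to two things: that the experimental arm gave a deliverable plan, and that "the experimental planning arm produced a plan determined to be acceptable as per institutional guidelines". Under Statistical analysis plan, patients are analysed by assigned arm, and for both efficacy rates "differences between treatment arms will be compared using the Chi-square test or Fisher’s exact test as appropriate".

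**The concern.** A diagnostic-CT plan that is undeliverable is by definition not the delivered plan, so the rule as fixed cannot score it. The patient either contributes no score or contributes the score of a plan made on that day's CBCT. The article describes this route for Arm 2 alone.

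Some of the listed reasons bear directly on what reviewers score. Set-up or contour variation that image guidance cannot correct, and a target that has outgrown its volume, are cases in which PTV coverage is likely to fall short. Removing or replacing them probably moves Arm 2's acceptability rate upward.

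At stake is the meaning of the one blinded efficacy comparison. It is presented as a comparison of two planning image sets. As defined, it compares CT-simulation plans with those diagnostic-CT plans that passed a check on the treatment unit, possibly together with CBCT plans.

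**Working it through.** **The plan's own figure.** The article gives no expected rate or sample size for acceptability. Its only sample size is for time in centre: 33 patients, 11 and 22. That figure reproduces. With a difference of 4.8 − 2.5 = 2.3 hours, SD 2 and two-sided alpha 0.05, the exact t-test has 81.0% power at 10 + 19 = 29 patients, and 29/0.9 = 32.2 rounds up to 33. The present point does not affect it.

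**Inputs.** Arm sizes of 11 and 22 come from Sample size calculation. The number u of undeliverable diagnostic-CT plans is unknown. The documents give two reference points: 100% deliverability in an earlier cohort of 30 (Background), and an interim threshold of 60% (Interim analysis/early trial discontinuation).

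**Bound on the shift.** Let D = 22 − u be the delivered diagnostic-CT plans, A the number of these scored acceptable, and r the number of CBCT back-up plans scored acceptable (r ≤ u).

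- Undeliverable plans left unscored: reported rate A/D.
- Undeliverable plans represented by back-up plans, one for each: reported rate (A + r)/22.
- Initially planned treatment delivered and acceptable: A/22.

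The first exceeds the third by A·u/(22·D), which is at most u/22 because A ≤ D. The second exceeds it by r/22, also at most u/22. With fewer than 22 evaluable patients, that number replaces 22.

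**The bound in numbers.** Assume that every delivered plan is acceptable, including any back-up plan, and that Arm 1 is 11/11. The delivered-plan rate in Arm 2 is then 100%, and Fisher's p is 1.00, in every row.

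| u | Delivered and acceptable (Clopper-Pearson 95% CI) | Shift, points | Fisher p against 11/11 |
|---|---|---|---|
| 0 | 22/22 = 100% | 0 | 1.00 |
| 1 | 21/22 = 95.5% | 4.5 | 1.00 |
| 3 | 19/22 = 86.4% (65 to 97%) | 13.6 | 0.53 |
| 4 | 18/22 = 81.8% | 18.2 | 0.28 |
| 8 | 14/22 = 63.6% (41 to 83%) | 36.4 | 0.031 |
| 9 | 13/22 = 59.1% | 40.9 | 0.015 |

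The row u = 8 lies just above the 60% interim threshold and u = 9 just below it.

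**Handling matters even when some delivered plans fail review.** Take u = 4 and A = 16 of 18. Leaving undeliverable plans unscored gives 16/18 = 88.9%. With four back-up plans, the rate is 18/22 = 81.8%, 19/22 = 86.4% or 20/22 = 90.9% as two, three or four of them are acceptable. Delivered-and-acceptable is 16/22 = 72.7%. The article does not say which handling applies. Nor does it say, for a patient treated on a back-up plan, whether the score uses the original matching CBCT or the repeat verification CBCT.

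**The case against.** The strongest reply is that the failures are already counted. Efficacy in the Background rests on deliverability and acceptability together, the two are listed as separate endpoints, and primary deliverability concerns the diagnostic-CT plan alone. With 8 of 22 undeliverable, 14/22 = 64% would be reported under that name, and the interim analysis watches the same rate. This stands. A reader might infer that the plan hides failed diagnostic-CT plans; it does not. The acceptability comparison itself nevertheless remains conditional.

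A reader might also infer a breach of intention-to-treat. The documents do not support that for the back-up branch. The Background makes CBCT planning part of the experimental workflow, so scoring a back-up plan in Arm 2 keeps the patient in the assigned arm. It measures the whole workflow rather than the planning image set. Likewise, nothing says that a back-up plan counts as a success for the diagnostic-CT plan; the text is silent.

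Third, acceptability is dosimetric. Two of the four reasons (changes that contraindicate treatment, and new findings that call for deferral) are clinical, and such a plan might meet every dose criterion. Declaring every undeliverable plan unacceptable would be a debatable choice of estimand. This also stands, and it is why the fix adds a combined rate instead of redefining acceptability.

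Fourth, denominators are often left to an analysis plan. That is fair for the handling of unscored patients. But the choice to score the delivered plan is fixed in this document, and the conditioning follows from it. The blinding reason is sound and does not require that undeliverable plans drop out of the comparison.

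**Conclusion.** The point holds as a matter of definition and reporting for a secondary endpoint. As written, the between-arm acceptability test is conditioned on deliverability in Arm 2 only and may include plans not made on the diagnostic CT.

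Relative to a delivered-and-acceptable rate, the upward shift is at most u/22. It is zero if all plans are deliverable, as in the earlier cohort of 30. This trial adds thoracic targets, so that result cannot simply be carried over. The tabulated figures are upper bounds on bias in dosimetric acceptability: they assume that all delivered plans are acceptable and treat every undeliverable plan as a failure, although some deferrals are clinical. The p-values also assume 11/11 in Arm 1. They illustrate how far the conclusion could move and are not forecasts.

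The separate deliverability rate limits the harm for a reader who takes both rates together. The change is worth making, but the point does not undermine the primary endpoint or the sample size.

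**What to change.** Keep the blinded review of the delivered plan, and make three changes:

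1. Split acceptability as deliverability is already split: scores for delivered diagnostic-CT plans and scores for CBCT back-up plans, reported separately. State which CBCT is used for the latter. A whole-workflow rate may be shown as well if it is labelled as such.
2. Add, as the between-arm efficacy comparison, the proportion of all randomised patients with a planned fraction 1 whose initially planned treatment (CT-simulation plan in Arm 1, diagnostic-CT plan in Arm 2) was both delivered and scored acceptable.
3. Tabulate the documented reasons for undeliverability, so that clinical deferrals can be told apart from dosimetric or set-up failures.

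The cost is mainly wording. Deliverability is already recorded as yes or no, and reasons must be documented for any undeliverable plan. Because the list of reasons stands only under Arm 2, it should be confirmed that the same yes/no item is completed in Arm 1. The sample size is unchanged. The downside for the sponsor is that Arm 2's headline rate may be lower.

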### Stakeholder acceptability

Acceptability of the intervention will be evaluated by patients and clinicians using a Likert scale modeled on the Theoretical Framework of Acceptability (version 2) [22]. These questionnaires have been reviewed for face validity by an expert panel including ROs, medical physicists, and radiation therapists. See Additional file 1: Appendix A for Questionnaire Items based on the Theoretical Framework of Acceptability.

#### Patient acceptability

Patient acceptability will be assessed immediately following treatment delivery.

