#### Clinician acceptability

Clinical acceptability will include all those involved in the treatment pathway and will be assessed within 5 working days of treatment delivery *for Arm 2 patients only*. Clinicians may be asked to complete the questionnaire up to 3 times to inform analysis as to whether perceptions change over time, for example, with increasing familiarity/exposure to the novel workflow.

Involved clinicians will be identified by the Collaborating Investigator or a member of the Lawson Health Research Institute Clinical Research Unit based on the electronic care path/treatment record.

On a clinician’s first encounter, an electronic version of the Clinician LOI/Consent will be emailed to their institutional email address. All staff will be aware of the possibility of receiving the LOI/Consent as they will be informed prior to opening the study at a staff meeting/inservice and by an email from the Principal and Collaborating Investigator. If/when the e-consent is completed and received, an e-version of the questionnaire will then be sent to the clinician.

Clinicians will be required to indicate how many times they have previously participated in the dCT-enabled treatment planning workflow on the questionnaire, but will only be required to complete one e-consent form. They will be advised of their right to withdraw participation at any time and for any reason, and that completing one questionnaire does not obligate them to complete further questionnaires.

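### Both acceptability questionnaires are timed only from treatment delivery, so an Arm 2 visit that ends with no beam has no assessment point, and Arm 2 patient acceptability may be biased upward

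*Protocol article*

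**What the plan says.** All places are in the Protocol article.

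- **Patient acceptability** gives one time point: "Patient acceptability will be assessed immediately following treatment delivery".
- **Clinician acceptability** gives one window, for Arm 2 only: it "will be assessed within 5 working days of treatment delivery". The same section sets a wide population, "Clinical acceptability will include all those involved in the treatment pathway", and identifies these people "based on the electronic care path/treatment record". A clinician may be asked up to three times.
- **Undeliverable plan** (under Arm 2) lists situations in which the diagnostic-CT plan cannot be used. Two of them point to no treatment that day: CBCT changes that contraindicate radiotherapy, and new findings "which warrant PRT deferral for further assessment or involvement of other services". The back-up is optional: "At the discretion of the RO, CBCT-enabled planning may be enacted if a diagnostic-CT-enabled plan is considered undeliverable".
- **Treatment delivery with CBCT plan** describes what follows if the back-up is used: "The patient can then be treated using the CBCT plan after repeat CBCT for verification".
- **Statistical analysis plan** analyses patients by assigned group and compares acceptability between arms with a chi-square or Fisher's exact test.
- **Objectives** names acceptability as one of the three things the trial assesses.

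**The concern.** The plan fixes when acceptability is measured, and the event it chooses is one that the plan itself expects sometimes not to happen. A patient who attends in Arm 2 and leaves untreated never reaches the trigger that day. If treatment is given later, the questionnaire follows that later delivery and no longer captures the reaction to the unsuccessful visit. The staff who worked on the attempt have no delivery date from which their five days can run.

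The loss would not be random. Whether a visit is rated depends on whether it ended in a delivered beam, which is close to asking whether the workflow under test worked. If the people at those visits view the workflow less favourably, the Arm 2 rating describes mainly the visits that went well. The trial would then report a more favourable answer on one of its three stated aims than all assigned patients would have given.

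**Working it through.** **1. Which Arm 2 visits reach the trigger?**

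| Course of the visit | Beam that day? | Patient survey as written |
|---|---|---|
| Diagnostic-CT plan delivered | Yes | Given |
| Plan undeliverable, CBCT plan used | Yes | Given |
| Plan undeliverable, deferred, treated later | No | Only after the later delivery |
| Plan undeliverable, never treated | No | No time point |

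Only the last two rows are affected. For clinicians, the population wording covers all four rows, but the five-day window starts only where there is a delivery.

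**2. Figures in the plan.** The article gives no expected acceptability rate and no expected rate of no-beam visits, so there is no figure on this point to reproduce. The sample size of 33 (11 and 22) is set for time in centre and is not affected. Only the 22 Arm 2 patients are used below.

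**3. Size of a possible bias in Arm 2.** Let k be the number of the 22 not surveyed about their visit, a the favourable share among those surveyed, and b the share among those missed.

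- Reported rate = a
- Rate in all 22 = [(22 − k)a + kb] / 22
- Overstatement = (k/22)(a − b)

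Assume a = 90%, with b = 50% or b = 0%:

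| k | Rate in all 22, b = 50% | Overstatement | Rate in all 22, b = 0% | Overstatement |
|---|---|---|---|---|
| 0 | 90.0% | 0 | 90.0% | 0 |
| 1 | 88.2% | 1.8 points | 85.9% | 4.1 points |
| 2 | 86.4% | 3.6 points | 81.8% | 8.2 points |
| 4 | 82.7% | 7.3 points | 73.6% | 16.4 points |

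For k = 2 and b = 0: (2/22)(0.90 − 0) = 0.082. If b = a, the overstatement is zero at every k.

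**4. How likely is such a visit?** Let u be the share of plans that are undeliverable and f the share of those without CBCT back-up. Both are assumed. The expected number is 22uf, and the chance of at least one is 1 − (1 − uf)^22.

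- u = 0: none.
- u = 5%, f = 50%: 0.55 expected; 1 − 0.975^22 = 43%.
- u = 10%, f = 50%: 1.1 expected; 1 − 0.95^22 = 68%.
- u = 20%, f = 50%: 2.2 expected; 1 − 0.90^22 = 90%.

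The Background cites 100% deliverability in a cohort of 30. Zero failures in 30 is compatible, at a one-sided 95% bound, with a rate up to 1 − 0.05^(1/30) = 9.5%, or about 2 of 22 before any back-up is used.

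**5. Between arms.** An Arm 1 patient found untreatable on the day would be missed in the same way. With k₁ missed of 11 in Arm 1 and the same a and b, the bias in the difference is (k/22 − k₁/11)(a − b). One missed patient in Arm 1 therefore offsets two in Arm 2.

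**The case against.** The strongest reply is that a sentence about timing is not an exclusion rule. Nothing in the article says that people from no-beam visits are left out, and an article leaves much operational detail to the full protocol. This stands against saying that these people will not be surveyed. It does not remove the point, because the article states the trigger itself, and an assessment meant to follow the visit immediately cannot be recovered later.

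Several stronger readings are tempting, and the documents do not support them.

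- *Every failed plan is lost.* Patients treated with the CBCT plan have a delivery and are surveyed, and so, later, are deferred patients who are eventually treated.
- *Staff from failed visits are excluded.* The Clinician inclusion criteria rest on taking part in an Arm 2 workflow, and Clinician acceptability covers all those involved, found from the care record. What may be lost is the response to that visit, not necessarily the clinician. No between-arm bias can arise here, since clinicians are surveyed for Arm 2 only.
- *Intention-to-treat is broken.* Nobody changes group. A questionnaire not given is missing outcome data, which weakens an analysis by assigned group but does not contradict it.
- *Arm 2 acceptability is overstated.* This needs at least one no-beam visit and less favourable views there. The article gives neither rate. A fracture or atelectasis found on the day is a clinical discovery, and the patient need not blame the planning method.
- *Eight or nine patients could be missing.* That takes 40% of 22 = 8.8 from the interim rule. But 60% deliverability is the level below which the team may recommend cessation or site exclusion. It is not a forecast, and the figure also assumes that the back-up is never used.

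Arm 1 also has a mandatory fraction 1 CBCT, so losses need not be confined to Arm 2. They are still more plausible there: the diagnostic scan may be up to 28 days old at enrolment, while Arm 1 is simulated on the treatment day.

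Finally, acceptability is a secondary endpoint with no stated threshold, and undeliverable plans remain visible through the deliverability endpoint and its documented reasons. That limits the consequence, but deliverability does not show how those visits were experienced.

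**Conclusion.** The point holds in a limited form. The only stated time points for both questionnaires depend on treatment delivery, and the plan itself foresees Arm 2 visits without one. Such visits have no defined assessment point, and whether a rating is missing depends on whether the workflow succeeded. An upward bias in Arm 2 patient acceptability is therefore possible, but not established.

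Its size cannot be fixed from the documents. It is zero with no such visits, about 2 to 4 points with one of 22, and about 4 to 8 points with two. These figures assume 90% favourable among those surveyed and 50% down to 0% among those missed. They treat a deferred patient who is surveyed only later as missed for the visit in question. The difference between arms would be biased less if Arm 1 loses patients in the same way. The sample size and the primary endpoint are not affected.

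**What to change.** - **Patient acceptability:** give the questionnaire at the end of the fraction 1 visit, before the patient leaves, in both arms and whether or not beam was delivered. In Arm 1 this should cover the whole same-day simulation and treatment visit, so that a patient found untreatable at simulation is also asked.
- **Clinician acceptability:** start the window of five working days from the fraction 1 appointment, attempted or completed. This brings the window into line with the population that the section already defines.
- **Reporting:** give the number of no-beam visits in each arm and show their ratings separately alongside the overall result.

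The cost is a wording amendment and a changed trigger for sending the questionnaire. No new instrument, visit or staff is needed, and no clinical rule is touched. The downside is that a few patients would be asked after a difficult visit and some may decline. Any who decline should be counted and reported.
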